## Abstract

**Objective::**

This clinical trial aims to establish whether TCM can promote the resorption of LDH and to assess the efficacy of such therapy for LDH, thereby evaluating its clinical effect.

**Methods::**

The present study design is for a single-center, 2-arm, open-label randomized controlled trial. A total of 150 eligible LDH patients will be randomly assigned to either a TCM treatment group or a control group in a 1:1 ratio. Patients in the TCM group will be administered a TCM decoction for 4 weeks. Patients in the conventional drug control group will be instructed to take a specific daily dose of celecoxib. The primary outcome measure is the change from baseline in the volume of the protrusion, as assessed using MR images. Secondary outcome measures include visual analog scale pain scores and Japanese Orthopaedic Association scores assessed at 3 and 6 months.

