##### Changes in protrusion size

2.12.1.1

MR images were assessed to measure changes in protrusion size. A 1.5-T MRI system (Siemens, Erlangen, Germany) was used with a spin-echo sequence. Eleven sections were scanned on T1- and T2-weighted sagittal views with an interlamellar spacing of 1.25 mm and a section thickness of 5 mm. The image data were scanned and processed by Picture Archiving and Communication Systems. The volume and resorption rate of the protrusion were calculated according to the method described by Autio.^[18]^ MRI scans were performed on the first visit, the second visit, and the final follow-up to calculate the volume of the protrusion (ie, baseline and 3- and 6-month follow-up). T2-weighted sagittal view MR image showing how the resorption rate is calculated.^[16]^ The internal boundary of the protrusion is the line connecting the posterior inferior margin of the upper centrum and the posterior superior margin of the lower centrum. The external boundary is the protrusion edge. A proficient MRI operator can determine the area of the protrusion, as shown in the right panel. The volume of the protrusion (mm^3^) = (inter-section spacing + section thickness) (mm) ×Σ area of the protrusion in each section (mm^2^). The resorption rate = (volume of protrusion before treatment—volume of protrusion after treatment/volume of protrusion before treatment) ×100(%). Representative images are shown in Figure 2.

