### Data analysis

2.14

Statistical analysis will be performed using SPSS 16.0. Measured data such as JOA scores and the volume of the protrusion will be compared using Student *t-*test for matched data; whereas enumerated data, such as the improvement in the JOA score, will be compared using the chi-squared test or Fisher exact probability test. *P* <.05 will be considered significant for all statistical tests.

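### The primary MRI outcome is not tied to one variable (volume change in mm³ or percentage resorption) or one time point, and the matched t-test named for volume does not compare the randomised arms

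*Protocol article*

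**What the plan says.** The plan addresses the primary MRI outcome in three places.

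- **Abstract, Methods.** "The primary outcome measure is the change from baseline in the volume of the protrusion, as assessed using MR images". One variable is named, with no time point.
- **Section 2.12.1.1, under 2.12.1 Primary outcome measure.** "The volume and resorption rate of the protrusion were calculated". A formula follows for each. The rate is printed as "The resorption rate = (volume of protrusion before treatment—volume of protrusion after treatment/volume of protrusion before treatment) ×100"; its bracket is misplaced, but the intent is clearly a percentage of the patient's own baseline. Scans are listed at "baseline and 3- and 6-month follow-up". Neither quantity and neither follow-up scan is singled out as primary.
- **Section 2.14 Data analysis.** "Measured data such as JOA scores and the volume of the protrusion will be compared using Student" t-test, described as a "test for matched data". The resorption rate is not mentioned.

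**The concern.** A volume change in mm³ and a percentage resorption weight patients differently. A herniation that shrinks from 3000 to 2400 mm³ loses 600 mm³, or 20%. One that shrinks from 500 to 100 mm³ loses 400 mm³, or 80%. The first patient does better on one scale and the second on the other.

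The trial asks whether TCM promotes resorption, and a result on either scale could be presented as the primary answer. If the choice is left open, it can be made after the data are seen, and the 5% error rate no longer holds. The test named in 2.14 adds a second problem: taken literally, it does not answer a between-arm question on any scale.

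This point is separate from the sentence in 2.13.1 that calls VAS the primary efficacy endpoint, and from the bracket slip in the rate formula. It remains after both are corrected.

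**Working it through.** **1. What the matched test tests.** Let d = volume after − volume before for each patient in one arm. The matched statistic is t = mean(d) / (SD(d)/√n). It tests whether mean change in that arm is zero. So the variable in 2.14 can agree with the abstract (mean change in volume). The comparison, however, is within patients. The introduction cites an overall resorption incidence of 66.66%, so shrinkage is expected in both arms. A significant matched test in the TCM arm would not show that TCM adds anything. The arms are independent groups, so no pairing links them.

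**2. The plan's own figure.** Section 2.13.3 gives α = 0.05, power 0.90, 75 per group and 15% dropout, but no effect size or SD. The total of 150 can therefore be neither reproduced nor refuted. Working backwards: 75 × 0.85 = 63.75, about 64 evaluable per arm; n = 2(1.960 + 1.282)²/d², so d = √(21.02/64) ≈ 0.573 (two-sided). This does not say on which scale the difference was meant, so the sample size does not settle the question.

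**3. How often the two scales disagree.** Simulated trials, 64 per arm, two-sided two-sample t-tests at 0.05 on each scale. From the protocol: only the 64 per arm and α. Assumed: lognormal baseline volume, median 1000 mm³, CV 40, 60 or 80%; and either proportional resorption (40% vs 55%, SD 27 points) or additive resorption (400 vs 550 mm³, SD 270).

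| Model | Quantity | CV 40% | CV 60% | CV 80% |
|---|---|---|---|---|
| Proportional | Power, change in mm³ | 67% | 52% | 39% |
| | Power, resorption rate | 87% | 88% | 87% |
| | Change and rate disagree on significance | 23% | 38% | 51% |
| | Power, ANCOVA with baseline volume | 82% | 77% | 69% |
| Additive | Power, change in mm³ | 85% | 83% | 79% |
| | Power, resorption rate | 72% | 62% | 52% |
| | Change and rate disagree on significance | 19% | 30% | 39% |
| | Power, ANCOVA with baseline volume | 85% | 83% | 80% |

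An independent rerun agreed within simulation error. The ranking of change and rate reverses between the two models, so neither scale is safe by default.

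A wider grid (CV 30–80%, control resorption 30%, TCM 40–54%, SD 20–30 points) gives disagreement between change and rate in 2–50% of trials with a true effect. Significant results in opposite directions for these two scales did not occur.

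**4. False-positive chance when either scale may be reported.** If each test has a 5% error, P(at least one significant) = 5% + half the disagreement rate. In the wider grid with no true effect, disagreement is 3–7%, giving 5 + 1.5 = 6.5% to 5 + 3.5 = 8.5%. Direct simulation under the assumptions of step 3 gives 7–9%. Allowing for other inputs, about 7–10% is a fair statement. This is for one time point; an open choice between 3 and 6 months would add to it and was not computed.

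**The case against.** The strongest reply is that all three places concern change in protrusion volume, that the abstract already names one variable, and that the scale of a change score may be left to a fuller document. Part of this stands. The abstract does not use the word absolute; mm³ is the natural reading, not a stated one. But the section that defines the primary outcome offers two quantities without ranking them, and 2.14 names a specific test that does not compare the arms. Those are statements in the text, not gaps left by condensation.

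A reader might infer more than the documents support:

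- *Three conflicting definitions, with plain follow-up volume in 2.14 as the third.* The sentence in 2.14 goes on to name a matched test, and on before-and-after volumes that is a test of mean change. An unpaired comparison of follow-up volumes is not described, so power or error figures built on it do not apply.
- *Often opposite conclusions.* Disagreement here means one P value below 0.05 and the other above it. Even if follow-up volume is included as a third option, significant results in opposite directions occur in at most 0.2% of simulated trials for any pair.
- *A large share of trials would change verdict.* The documents contain no volume data, and 2–50% is too wide a range for a flat statement.

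It is also fair to say that making the rate secondary is a choice, since the objective speaks of resorption. Following the abstract is the smallest change; what matters is that one variable is fixed.

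**Conclusion.** The point holds in a limited form. The primary MRI variable is not fixed to one scale or one time point, and the test in 2.14 addresses within-patient change and not the difference between randomised arms. Both follow from the text alone.

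The numerical consequence depends on assumed volumes and effects: significance differs between mm³ change and percentage resorption in roughly 2–50% of trials with a true effect, and the false-positive chance rises from 5% to about 7–10% if either may be reported. The documents support neither a claim of contradictory directions of effect nor a single figure for how often the verdict would change.

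**What to change.** In 2.12.1.1 and 2.14:

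1. State one primary variable, as the abstract does: change from baseline in protrusion volume (mm³).
2. State one primary time point, either 3 or 6 months, and treat the other as secondary.
3. Replace the matched t-test for this outcome with a between-arm ANCOVA with baseline volume as covariate. With baseline in the model, using follow-up volume or change as the response gives the same treatment effect.
4. List the resorption rate as a secondary outcome.

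Cost: wording in two sections and one covariate already measured; no extra patients, scans or visits. Under the assumed inputs ANCOVA is never materially worse than unadjusted change (additive: 85/83/80% against 85/83/79%) and clearly better when resorption is proportional (82/77/69% against 67/52/39%). The downside is small: the rate can no longer be claimed as the primary result, and if resorption is truly proportional it would have had somewhat more power, about 87% against 69–82%.

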**Discussion::**

The design and methodological rigor of this trial will allow evaluation of the basic clinical efficacy and safety data for TCM in the treatment of patients with LDH. The trial will also assess whether TCM can promote the resorption of LDH. This research will therefore help provide a solid foundation for the clinical treatment of LDH and for future research in TCM therapy.

**Trial registration::**

ChiCTR1900022377.

## Methods

2

### Study design

2.1

This clinical trial will be a randomized, controlled trial. Subjects will be enrolled at Suzhou Hospital of TCM. The Ethics Boards of Suzhou Hospital of TCM have approved this study. All study participants will give written informed consent before participation.

### Ethics approval and consent to participate

2.2

The study is in compliance with the Declaration of Helsinki. Only clinicians holding the necessary qualifications are acting as principal investigators. The final amendments (version: April 06, 2019) and the consent form have been reviewed and approved by the Ethics Committee of Suzhou hospital of TCM (reference number: SZTCM2019-4-01). If there is any amendment to the protocol, approval must be again sought from the Ethics Committee. Written informed consent will be obtained from each participant before enrolment.

### Inclusion criteria

2.3

(1)In this trial, we refer to the literature^[9,15–17]^ and set the inclusion criteria as follows: (1) age 20 to 60 years;(2)pain intensity ≥40 mm on the 100-mm pain visual analog scale (VAS) for lower back pain;(3)having low back pain and/or radiating pain from the lower extremities caused by LDH (MRI scan confirmed lumbar disk herniation in our hospital in the previous 2 weeks);(4)willing to participate in this study and giving informed consent;(5)written consent provided to participate in 2 follow-up MRI scans (at 3 months and 6 months).

### Exclusion criteria

2.4

In this trial, we refer to the literature^[9,15–17]^ and set the exclusion criteria as follows:

(1)red flag signs that may indicate cauda equina syndrome, such as bladder and bowel dysfunction or saddle anesthesia;(2)a history of spinal surgery;(3)having serious chronic diseases that could interfere with the outcomes;(4)pregnant or planning to become pregnant during the study;(5)having other diseases that the researchers believe render the subject unsuitable for the study;(6)patients whose MRI scans were low resolution or unsuccessful.

### Recruitment

2.5

Participants will be recruited through advertisements in local newspapers, bulletin boards, and on the websites of local medical centers. All patients will be screened initially to establish a baseline assessment of selection criteria. If the inclusion criteria are met and the informed consent form is signed, the patient will be submitted for randomization.

### Randomization

2.6

In this trial, participants will be randomly assigned to either the TCM group or the control group in a 1:1 ratio using a random number generator (SPSS 16.0, SPSS Inc, Chicago, IL).

### Blinding

2.7

Because the study will be an open-label clinical trial, both patients and clinicians will know which treatment is being administered, and patients are required to cooperate with their physicians prior to treatment. The assessment of clinical efficacy will be carried out by telephone by a clinical assessor who will be masked to the treatment assignment. During the data collection and analysis stages, the clinical researchers, assessors, and statisticians will not share study information.

### Intervention

2.8

This study will be conducted in accordance with the requirements outlined in the Declaration of Helsinki, and with the approval of the appropriate Institutional Review Boards. Each participant will sign the written informed consent form before undergoing any examination or study procedure, in compliance with Good Clinical Practice. Eligible patients will be randomized into 1 of the 2 groups: the TCM treatment group and the control group. Follow-up will be carried out by telephone inquiry and outpatient reexamination, which will be performed 3 and 6 months after the first visit. VAS and Japanese Orthopedic Association (JOA) scores will be recorded at each follow-up visit. MRI investigations will be performed on the first visit and at the 3-month and final follow-up to calculate the volume of the protrusion (Fig. 1).

**Figure 1 F1:**
[figure not shown]
Flowchart for participant identification, inclusion, study design, interventions, assessments, and follow-up.

### TCM treatment group

2.9

(1)Absolute bed rest is required for 4 weeks. Once permitted to ambulate, the patient is to wear a girdle for 4 to 8 weeks.(2)The patient is to take the following TCM preparation: (raw *Astragalus* 20 g, roasted *Astragalus* 20 g, Radix *Stephaniae tetrandrae* 10 g, *Angelica sinensis* 10 g, *Ligusticum wallichii* 10 g, Rhizoma *Atractylodis macrocephalae* 10 g, *Lumbricus* 10 g, leech 6 g, Radix Clematidis 10 g, pawpaw 10 g, and *Brassica alba* Boiss. 6 g decocted in 500 ml water and taken orally at a dosage of 300 mL/d for 4 weeks.(3)The patient is to perform the following exercises for 12 to 24 weeks:I.20 to 30 repetitions of 5-point support, in which the patient assumes a supine position and raises the abdomen and pelvis as high as possible for 3 s while supporting the body with the head, elbows, and feet. These actions are to be carried out 3 times a day.II.10 to 20 repetitions of swallow style, in which the patient assumes a prone position with the hands behind the back and raises the head and chest for 3 to 5 s while pushing the thighs back. These actions are carried out 3 times a day.

### Control group

2.10

Patients in the control group receive 4 weeks of normal conservative treatment. Intervention measures fall into 4 sections:

(1)Health education. Patients are invited to receive LDH health education twice a week in an outpatient setting; the health education is designed exclusively to inform patients about the natural course of their illness and the expectation of successful recovery, irrespective of the initial intensity of their pain. Patients will be educated to avoid some bad habits that aggravate the disease, such as remaining in the sitting position for a long time and carrying heavy loads. Patients are encouraged to participate in social activities.(2)Absolute bed rest is required for 4 weeks. Once ambulation is permitted, the patient is to wear a girdle for 4 to 8 weeks.(3)For the first 4 weeks, if the pain is not relieved, the patient may take 0.1 g b.i.d. of celecoxib.(4)The patient is to perform the following exercises for 12 to 24 weeks:1.20 to 30 repetitions of 5-point support, in which the patient assumes a supine position and raises the abdomen and pelvis as high as possible for 3 s while supporting the body with the head, elbows, and feet. These actions are carried out 3 times a day.2.10 to 20 repetitions of swallow style, in which the patient assumes a prone position with the hands behind the back and raises the head and chest for 3 to 5 seconds while pushing the thighs back. These actions are repeated 3 times a day.

### Indications for surgery

2.11

Surgery will be indicated if:

(1)after the termination of all interventions, conservative treatment with the TCM regimen for 3 to 6 months has been ineffective (Japanese Orthopaedic Association scores <16); or(2)the patient experiences exacerbation or progression of radicular symptoms or cauda equina neurological signs at any stage during the treatment period.

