#### JOA score

2.13.2

The JOA score indicates the severity of clinical symptoms. The improvement in JOA score is calculated according to the following equation:^[16]^ Improvement according to JOA score (%) = (score after completion of treatment − score before treatment)/ (29 − score before treatment) × 100 (the maximum possible score is 29). An improved JOA score ≥75% was classified as excellent, 50% to 75% as good, 25% to 50% as fair, and <25% as poor. The JOA score will be measured during each assessment visit (ie, at baseline and 3- and 6-month follow-up).

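### Section 2.11 ties the JOA <16 surgery indication to failure of the TCM regimen and gives controls no matching criterion, so as written the surgery rule differs by arm

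*Protocol article*

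**What the plan says.** Indications for surgery (2.11) lists two criteria. The first applies when "after the termination of all interventions, conservative treatment with the TCM regimen for 3 to 6 months has been ineffective", with failure defined as a JOA score below 16. The second applies when "the patient experiences exacerbation or progression of radicular symptoms or cauda equina neurological signs at any stage during the treatment period".

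The arms are described separately. For controls (2.10): "Patients in the control group receive 4 weeks of normal conservative treatment". In the TCM group (2.9) the decoction is "taken orally at a dosage of 300 mL/d for 4 weeks". Bed rest, girdle and exercise are the same in both arms; for the exercise, section 2.10 says "The patient is to perform the following exercises for 12 to 24 weeks", and section 2.9 gives the same duration.

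On timing, section 2.8 says "MRI investigations will be performed on the first visit and at the 3-month and final follow-up to calculate the volume of the protrusion", and section 2.13.2 says "The JOA score will be measured during each assessment visit (ie, at baseline and 3- and 6-month follow-up". Under Blinding (2.7), "both patients and clinicians will know which treatment is being administered".

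**The concern.** Take two patients, one per arm, who have finished all treatment, have a JOA score below 16 and are stable. The TCM patient meets criterion (1). The control does not, because that criterion names only the TCM regimen, and does not meet criterion (2) either, because nothing is worsening. Clinicians who know the allocation and follow the text would have a stated reason to operate on one and not on the other.

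Surgery acts directly on the primary outcome, the volume of the protrusion. If it is offered by arm after randomisation and before a scheduled scan, the comparison at that scan mixes the effect of treatment with the effect of the surgery rule. Randomisation does not protect against this.

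**Working it through.** **No stated figure to reproduce.** The point rests on wording. The document gives no surgery rate, no expected resorption and no SD. The check therefore has two parts: when criterion (1) can act, and what an imbalance would do under declared assumptions.

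**1. When criterion (1) can act** (durations from 2.9 and 2.10; 3 and 6 months taken as weeks 13 and 26)

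- Decoction: ends at week 4.
- Bed rest 4 weeks, then girdle 4 to 8 weeks: ends at weeks 8 to 12.
- Exercise 12 to 24 weeks: ends at weeks 12 to 24 if begun on day 1, or weeks 16 to 28 if begun after bed rest (4 + 12 to 4 + 24).

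Criterion (1) requires all interventions to have ended, so it opens at weeks 12 to 24 or weeks 16 to 28. JOA is scheduled only at about weeks 13 and 26. It follows that:

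- If everything has ended by week 13, failure can be found at the 3-month visit, leaving 26 - 13 = 13 weeks before the final MRI.
- If interventions end between weeks 13 and 26, surgery before the final MRI needs an unscheduled JOA assessment.
- If failure is first found at the 6-month visit, the final MRI is due at that same visit.
- The 3-month volume is largely unaffected, because MRI and JOA are both due then and criterion (1) opens at week 12 at the earliest.

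**2. Illustration of size (assumed inputs, not from the document)**

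Evaluable patients: 75 x 0.85 = 63.75, taken as 64 per arm (numbers from 2.13.3). Assumed in both arms: mean resorption 35%, SD 30 points, no true difference. Also assumed: correlation 0.3 between failure and low resorption, and 80% resorption on a post-operative scan. Operated patients are the k with the highest failure propensity among 64.

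For k = 6, the mean of the top 6 of 64 standard normal values is 1.74, so the expected resorption of these patients without surgery is 35 - 30 x 0.3 x 1.74 = 19.3%. With 6 TCM and 0 control operations, the shift in the 6-month difference (TCM minus control) is:

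- post-operative scans counted: 6 x (80 - 19.3)/64 = +5.7 points;
- operated patients excluded: 6 x (35 - 19.3)/58 = +1.6 points;
- operated patients scored as 0%: -6 x 19.3/64 = -1.8 points.

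Per operation (divide by 6) this is +0.95, +0.27 and -0.30. For k = 1, 3 and 6 with SD 25 to 40, correlation 0 to 0.6 and post-operative resorption 50 to 100%, the ranges per operation are 0.2 to 1.9, 0 to 0.9, and -0.55 to +0.33.

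False claims favouring TCM (nominal 2.5%; two-sample t-test at two-sided 5%; 60,000 simulated trials per scenario):

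| Operations, TCM v control | Counted | Excluded | Scored 0% |
|---|---|---|---|
| 3 v 0 | 7.5% | 3.7% | 1.5% |
| 6 v 0 | 17.3% | 4.9% | 0.8% |
| 6 v 3 | 6.0% | 3.5% | 1.2% |

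With equal numbers (3 v 3, 6 v 6) the shift is about 0 and the rates are about 2.5% or below under all three handlings. A repeat run agreed with the table to within about 0.2 percentage points.

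**The case against.** The strongest reply is that this is a slip of wording. A regimen of 3 to 6 months cannot be the 4-week decoction; the only component of that length is the exercise, which both arms receive. Section 2.11 also stands apart from the two treatment sections and opens by referring to all interventions. The slip is plausible, but treating clinicians work from the text as written, and a correction costs almost nothing.

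The second reply is that the window is narrow. This stands. Surgery before the final MRI needs either all interventions to end by about week 13 or an unscheduled JOA assessment. If exercise follows the 4 weeks of bed rest, the 3-month visit cannot trigger criterion (1) at all.

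The third is that the size is assumed. This stands too. The larger error rates arise only if post-operative scans count as resorption. How such scans are handled may sit in an analysis plan that is not shown, so its absence from the article is no fault.

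Two stronger readings do not hold. A reader might infer that controls are barred from surgery: section 2.11 lists indications and prohibits nothing, and criterion (2) covers controls, so zero control operations is an assumption of the illustration. A reader might also infer that the rule favours TCM: the sign changes with the handling of operated patients, and the document settles neither that nor the number of operations.

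**Conclusion.** The point holds as a defect in a stated rule. Criterion (1) is specific to one arm, controls have no counterpart, and criterion (2) does not fill the gap for a stable patient who has failed treatment. That much is certain from the text and needs no assumption.

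The consequence is conditional. The 6-month protrusion volume could be biased if interventions end before the 6-month visit, failure is found by then, and clinicians follow the wording. Neither the direction nor the size can be found from the document. The shifts of about +1.0, +0.3 and -0.3 points per excess operation show scale only and rest on the assumed inputs above. The correction is worth making before recruitment proceeds, but this is not evidence that the trial's result will be biased.

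**What to change.** Make two wording changes in section 2.11.

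- **Criterion (1):** replace the reference to the TCM regimen with 'the assigned conservative treatment, in either arm'. Keep the JOA <16 threshold and the condition that all interventions have ended, the same in both arms.
- **Criterion (2):** state that it applies in either arm from randomisation to the 6-month visit, in place of the undefined treatment period.

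The cost is the two edits; no extra patients, visits or scans are needed, and the clinical decision stays with the investigators. The change removes the arm-specific rule. It does not guarantee equal surgery rates, since efficacy may differ and clinicians are unblinded.

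Two further steps may suggest themselves but are not recommended. Judging failure at 3 months whether or not interventions have ended would contradict the existing condition and make patients surgical candidates while still in prescribed exercise. Bringing the final MRI forward for operated patients would mean that their volume is no longer measured at 6 months.
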